## 4.2 Immunogenicity assessments

### 4.2.1 Sera storage

Sera samples will be collected and stored for evaluation of antibody responses that will be decided at a later stage, but prior to unblinding of laboratory personnel.

### 4.2.2 Cellular responses

Primary cellular responses will be assessed using the ELISpot assay on frozen specimens according to standardised operating procedures (SOPs) in a single accredited laboratory (CHUV), subject to ongoing quality control. The ELISpot reaction per well will be measured in an automated system, according to operating procedures that define the validity of the assay. All specimens will be sent to CHUV for the primary analysis.

CD4 and CD8 T cell responses will be assessed by flow cytometry on frozen specimens according to standardised procedures in a centralised INSERM laboratory at Créteil (CHU Henri Mondor). All specimens will be sent to CHU Henri Mondor for flow cytometry analyses. T-cell responses will be evaluated by the percentages of cells producing IL-2 and/or IFN- $\gamma$  within CD4 and CD8 T cell populations after 18 hours of ex-vivo stimulation of PBMCs with HIV-1 peptide pools. HIV-1 clade C peptide pools will be provided by Eurovacc. Flow cytometry analyses will be performed at weeks 26, 28, 48 and 72.

### 4.2.3 Store for HLA testing

A store will be collected at week 4 to perform HLA typing in case this is required to assist future evaluation of the cellular responses.

## 4.3 Other assessments

### 4.3.1 HIV antibody test

Samples will be tested in the laboratories local to the clinical centre using ELISA, according to standard procedures subject to quality control.

### 4.3.2 Pregnancy test

A pregnancy test will be performed by analysis of a urine sample for Human Chorionic Gonadotrophin (HCG) collected from female participants at screening and on the day of each immunisation. The analysis will be conducted by a member of the study team according to trial specific standardised operating procedures.

#### 4.3.3 Genital infection

The assays will be conducted in laboratories local to the clinical centre, according to standard procedures subject to quality control.

#### 4.3.4 Following adverse event

Other assessments may be performed as clinically indicated due to an adverse event.

#### 4.3.5 Concomitant medication

Participants will be asked about medication taken at each visit up to and including week 48, and this will be recorded in the case record form. It is expected that the name of the drug, indication for use, dose, frequency, start and stop dates will be available for prescription-only medication, either from the participant or from the prescribing physician. For medication available over the counter, the maximum information available on questioning the participant will be recorded.

## 5 Adverse events

### 5.1 Definitions

An adverse event is any adverse experience occurring during the course of the study from screening visit.

Criteria for grading clinical and laboratory events are listed in appendix 4.

A severe adverse event is one **graded 3 or 4** by criteria in appendix 4. Some, but not all grade 3 and 4 adverse events will be “serious” by ICH GCP criteria below.

#### 5.1.1 Serious Adverse Events (SAEs)

An adverse event is considered to be a “serious adverse event” by ICH Good Clinical Practice (ICH GCP) criteria if it results in the following:

- death,
- a threat to life,
- requires in-patient hospitalisation or prolongs existing hospitalisation (hospitalisation for elective treatment of a pre-existing condition is not included),
- results in persistent or significant disability or incapacity,
- is a congenital anomaly (ie, the outcome of pregnancy involving a participant), or
- is any other important medical condition\*.

\*Examples of conditions regarded as “any other important medical condition” include allergic bronchospasm requiring intensive emergency treatment, seizures or blood dyscrasias which did not result in hospitalisation or development of drug dependency.

### 5.2 Relationship to study product

This can be classified as:

|                       |                                                                                                                                                                                                                     |
|-----------------------|---------------------------------------------------------------------------------------------------------------------------------------------------------------------------------------------------------------------|
| Unrelated      | adverse events that can be clearly explained by extraneous causes and for which there is no plausible association with study product, or adverse events for which there is no temporal relationship                 |
| Unlikely to be | adverse events that may be temporally linked, but which are much more likely to be due to other causes than study product and which do not get worse with continuing use of product                                 |
| Possibly       | adverse events that could equally well be explained by study product or other causes, which are usually temporally linked and may improve when not using study product but do not reappear when using study product |
| Probably       | adverse events that are temporally linked and for which the study                                                                                                                                                   |

**Definitely** product is more likely to be the explanation than other causes, which may improve when not using study product  
 adverse events that are temporally linked and for which the study product is the most likely explanation, which disappear or decrease when not using study product and reappear when using study product

### 5.3 Reporting adverse events

Adverse events should be recorded on the appropriate case record form and reported to the MRC CTU (EuroVacc centres) or the INSERM U593 CTU (ANRS centres).

Any event resulting in discontinuation of the vaccination schedule should be reported within 2 working days of the decision to discontinue to the MRC CTU, INSERM U593 CTU, the Sponsors.

All SAEs should be reported to the MRC CTU, INSERM U593 CTU the same working day that the Clinical Investigator becomes aware of the event fulfilling the above criteria. This can be done by telephone or fax. The minimum criteria required in reporting a SAE are the participant identifiers (trial number/date of birth/initials), reporting source (name of Investigator), why the adverse event is identifiable as serious.

**The adverse event reporting telephone number is**  
**EuroVacc centres - [contact] and [contact]**  
**ANRS centres - [contact] [contact]**

They will also be immediately reported to principal investigators by the CTUs.

Any SAE that is considered possibly, probably or definitely related to study product will be unexpected and as such qualify for expedited reporting to the regulatory authority.

Staff at the MRC CTU/ANRS Pharmacovigilance will confirm that the event qualifies in grade and relationship as a Suspected Unexpected Serious Adverse Drug Reaction (SUSAR) and arrange for multi-disciplinary review of the case to take place within 3 working days when the event is suspected to be possibly, probably or definitely related to study product. Those involved in this review will include the site Clinical Investigator, the medical expert at MRC CTU/ANRS pharmacovigilance and a panel of individuals with the expertise in quality and preclinical aspects of the vaccines and to the clinical responses to immunogens. The report will be prepared by the MRC CTU Medical Expert or their deputy (EuroVacc centres) or a physician from the ANRS Pharmacovigilance team (ANRS centres) and filed with the appropriate regulatory authorities, Ethics committees, and Eudravigilance, within the timelines required by national legislation. MRC CTU and INSERM U593 CTU will be responsible for sending a copy of the report to their other respective clinical centres involved in the programme and to inform the full Trial Coordinating and Data and Safety Monitoring Committees, the EuroVacc Foundation, Sanofi Pasteur and Cobra. For EuroVacc centres, the site Clinical Investigator is responsible for notifying their Local Research Ethics Committee. For ANRS centres; ANRS pharmacovigilance team will notify the Ethics Committee. The detailed process for the reporting and filing of SUSARs to the EMEA (Eudravigilance), the relevant regulatory authorities and the Ethics Committee, as well as the writing of the annual safety report will be further defined in a SOP.

Examples of SAEs that do not require expedited reporting include:

- ◆ Hospitalisation for scheduled surgery unrelated to vaccine, other than temporally (within 30 days)
- ◆ Orthopaedic or traumatic injuries requiring hospitalisation
- ◆ Hospitalisation planned for pre-existing conditions not due to an aggravation in the condition
- ◆ SAEs occurring more than 30 days after vaccination and that are expected not related to the vaccine or having appeared before vaccination without any

aggravation after vaccination

These must be prioritised for data entry and the site Principal Investigator is responsible for ensuring that the completed SAE case record form reaches data entry within 10 working days of becoming aware of the event.

## **5.4 Clinical management**

Events will be managed by the clinical trial team who will assess and treat the event as appropriate, including referral to an independent physician and/or the participant's General Practitioner if required. There will be clinical operating procedures in place for the management of abnormalities detected following urinalysis or routine laboratory tests.

### **5.4.1 Recommendations for discontinuation**

Discontinuation of the study vaccine schedule due to an adverse event is at the discretion of the site Principal Investigator or their Medical Deputy, but would be recommended in the event of a grade 3 or 4 clinical or laboratory event (confirmed on examination or repeat testing respectively) which did not resolve within 72 hours. There must be no further immunisations following:

- 1) extensive, indurated redness and swelling involving the major circumference of the arm or thigh, not resolving within 72 hours or
- 2) fever  $\geq 39.5^{\circ}\text{C}$  within 48 hours; anaphylaxis; bronchospasm; laryngeal oedema; collapse; convulsions or encephalopathy within 72 hours

## **6 Management of HIV issues during and following the trial**

### **6.1 HIV testing**

Only volunteers with a negative HIV ELISA result will be enrolled. A risk assessment will be undertaken prior to the NYVAC-C immunisations and if risk status has changed then immunisation may have to be delayed until the HIV status of the participant is clarified. It is possible that participants may develop antibodies and test 'positive' in routine HIV ELISA assays subsequent to immunisation. Accredited laboratories local to each clinical centre will conduct any additional tests to distinguish between infection and a post-immunisation response required either for clinical management, or at the request of a participant. Entry and week 48 samples will be collected and tested in real-time so that participants can be informed of the result and a plan to recall and retest them made should this be necessary. In the event of ongoing post-immunisation positive ELISA, the participants will be invited to reattend annually until such time as this response has disappeared, and provided with an explanatory identity card in the interim.

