## II Summary of Trial

140 healthy volunteers at low risk of HIV infection will be entered into the study to receive one of the following regimens:

|                                | Wk 0                                                       | Wk 4                                                       | Wk 8                                                       | Wk 20                                             | Wk 24                                             |
|--------------------------------|------------------------------------------------------------|------------------------------------------------------------|------------------------------------------------------------|---------------------------------------------------|---------------------------------------------------|
| group 1
"DNAx3"

n=70 | DNA-C
2x2ml IM
right and left
vastus
lateralis | DNA-C
2x2ml IM
right and left
vastus
lateralis | DNA-C
2x2ml IM
right and left
vastus
lateralis |                                                   | NYVAC-C
1 ml IM
Non-
dominant
deltoid |
| group 2
"DNAx2"

n=70 | DNA-C
2x2ml IM
right and left
vastus
lateralis | DNA-C
2x2ml IM
right and left
vastus
lateralis |                                                            | NYVAC-C
1 ml IM
non-
dominant
deltoid | NYVAC-C
1 ml IM
Non-
dominant
deltoid |

Participants will attend the clinical centre on at least 14 occasions over 72 weeks. These visits will comprise:

- Screening
- Enrolment, trial entry and first immunisation
- Second immunisation
- Third immunisation
- Fourth immunisation
- Early follow-up after each immunisation
- Two other follow-up for safety and immune responses
- Week 48 final safety visit
- Week 72 immune responses

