**2.4 Follow-up visits**

Assessments and procedures will be performed according to schedules in 2.6.

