**2.5 Final visit**

Assessments will be undertaken according to schedules in 2.6.

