| Cell storage                           |     | X |           | X         |           | X         |           | Group 1    | Group 2    |            | X          | X          | X          | X         | X          |
| Diary card e                |     | ↔ |           | ↔         |           | ↔         |           | ↔          |            | ↔          |            | ↔          |            |           |            |

aincluding weight in kg, height in cm and arm & thigh circumference in cm

bincluding serology for syphilis, hepatitis B and C at screening. Genital swabs or urine for Neisseria gonorrhoea, chlamydia trachomatis and trichomonas vaginalis will be collected if indicated according to clinical standardised operating procedures (SOPs).

c additional HIV/STI and pregnancy tests will be performed if indicated by a change in risk status or menstrual history respectively

dHLA genotyping will be performed for evaluation of epitopic responses in responders; serological assays to be determined at a later stage, but prior to unblinding of laboratory personnel

ediary card will be completed for at least 1 week following immunisation

fCD4 number and % only at this visit

(x) means that a specimen will be collected only if indicated on history

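### The study schedule omits the week-48 HIV antibody test that section 6.1 promises, and places the only routine post-vaccination test at week 28

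*Protocol*

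**What the plan says.** Section 6.1 (HIV testing) warns that vaccinated participants may test positive on routine HIV ELISA. It then commits to two testing points: "Entry and week 48 samples will be collected and tested in real-time so that participants can be informed of the result", with "a plan to recall and retest them made should this be necessary". For those who stay positive it adds: "In the event of ongoing post-immunisation positive ELISA, the participants will be invited to reattend annually". Week 28 does not appear in the section.

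The HIV antibody row in section 2.6 (EV03 Study schedule) has three entries: a test at screening, a bracketed entry at week 20 and a test at week 28. The table's key says a bracketed entry is collected only if the history calls for it. The week-48 and week-72 cells are empty. Footnote c, attached to this row, says "additional HIV/STI and pregnancy tests will be performed if indicated by a change in risk status or menstrual history respectively".

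Sites are sent to this table for visit content. Section 2.4 (Follow-up visits) reads "Assessments and procedures will be performed according to schedules in 2.6", and section 2.5 (Final visit) reads "Assessments will be undertaken according to schedules in 2.6". The Summary of Trial lists the "Week 48 final safety visit" among the visits.

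**The concern.** Two current sections give different weeks for the routine HIV test after vaccination, and nothing in the protocol reconciles them. A clinic that builds its week-48 visit from the schedule would draw the safety bloods, repeat the examination and take no HIV test. The participant would then leave the final safety visit without the result that section 6.1 says they will be given.

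The two weeks are not interchangeable. A test soon after the last NYVAC-C dose shows whether vaccination has produced an early positive ELISA. It cannot show whether that result has lasted, and the invitation to return annually applies only to an ongoing positive. Nor can a week-28 sample reveal an infection acquired later. These are healthy HIV-negative volunteers, and section 6.3 relies on HIV testing and certification to limit social discrimination. Missing the later test weakens that protection, and if some sites act on section 6.1 and others on section 2.6, practice will differ between centres.

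**Working it through.** The protocol gives no figure to reproduce here. The check sets the two sections side by side, confirms that the table has been read correctly, and works out the timing.

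**Test weeks in each section**

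| Time | Section 2.6, HIV antibody row | Section 6.1 |
|---|---|---|
| Screening/entry | Test | Test, real time |
| Week 20 | Only if indicated on history | Risk assessment before NYVAC-C; no routine test |
| Week 28 | Test | Not mentioned |
| Week 48 | Blank | Test, real time |
| Week 72 | Blank | Not mentioned |

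**Is the table read correctly?** The header has 15 visit columns and the HIV antibody row has 15 visit cells, with entries in columns 1 (screening), 9 (week 20) and 13 (week 28). Column 14 (week 48) is empty. Other rows read in the same way agree with the text:

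- Flow cytometry falls at weeks 0, 26, 28, 48 and 72. Section 4.2.2 says "Flow cytometry analyses will be performed at weeks 26, 28, 48 and 72", which matches every post-vaccination entry.
- HLA cell storage falls at week 4, as in section 4.2.3.
- The HIV risk screen falls at week 20, which fits the risk assessment before NYVAC-C in section 6.1.
- History and examination carries an entry at week 48 but not at week 28; the CD4 row carries one at week 28 but not at week 48.

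The two columns are therefore distinct, and the HIV entry sits in the week-28 column.

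**Does another provision supply a routine week-48 test?**

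- Footnote c of section 2.6 adds HIV tests only on a change in risk status.
- Sections 6.1 and 6.1.1 add tests for clinical management or at the participant's request.
- Section 4.3.1 describes the assay but names no weeks.
- Serum is stored at week 48, but section 4.2.1 reserves it for antibody assays to be chosen later, which is not real-time HIV testing.

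Section 6.1 is the only source of a routine week-48 test.

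**Timing after the last dose.** Section 2.6 gives windows of ±1 week at week 24 (last NYVAC-C dose in both groups), ±1 week at week 28 and ±2 weeks at week 48.

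- Last dose to scheduled test: 28 − 24 = 4 weeks. Shortest 27 − 25 = 2; longest 29 − 23 = 6.
- Last dose to promised test: 48 − 24 = 24 weeks. Shortest 46 − 25 = 21; longest 50 − 23 = 27.

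Even at the extremes of the windows, at least 21 − 6 = 15 weeks separate the two ranges, so a week-28 sample cannot stand in for a week-48 one.

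**The case against.** The best counter-argument is that section 6.1 is itself binding and unconditional. Section 9 obliges sites to abide by the whole protocol, not only the table, and a site that follows both sections simply tests at weeks 28 and 48. The table is also not a complete list. Section 4.3.5 asks about medication at each visit up to week 48 with no corresponding row, and section 4.3.2 requires a pregnancy test at screening that the schedule does not mark. A blank cell need not mean that a procedure is excluded.

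This shows that the omission is not certain to occur, and that point stands. It does not remove the conflict: sections 2.4 and 2.5 name the schedule as the source of visit content, and section 6.1 says nothing of week 28, so it does not read as an addition to the table.

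A second argument is that parts of the table look damaged in the available copy. The diary-card arrows fall partly at weeks without an immunisation, and footnote f has no visible marker. That is a fair caution, but the rows that bear on weeks 28 and 48 agree with the text and show no shift.

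Third, there are safeguards: the week-28 test, further tests on request or on a change of risk, an identification card, and a return visit at week 72. These reduce the harm, but none is a routine late test. Two limits also stand. Section 6.1 does not itself name week 48 as the test of persistence; that follows from the timing. The participant information sheet is not available here, so what volunteers were told about test weeks cannot be checked.

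**Conclusion.** The concern holds. The schedule and section 6.1 disagree on when the routine post-vaccination HIV test takes place, and a site that follows the schedule would omit the one section 6.1 promises. Up to 140 participants are exposed; that is the planned enrolment, not an estimate of how many would actually miss the test. The practical difference is a last routine test at 2 to 6 weeks after the final dose instead of 21 to 27 weeks.

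The conclusion rests on the schedule being correctly aligned in the available copy, which the neighbouring rows support, and on sites using section 2.6 as sections 2.4 and 2.5 direct. The protocol does not show which of the two weeks was intended, but as written at least one section is wrong or incomplete. The consequence is for participant information, counselling and follow-up. The primary immunogenicity analysis, sample size and error rates are untouched. The point should be corrected.

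**What to change.** Mark the HIV antibody test at week 48 in section 2.6. Then settle week 28: if that test is wanted, add it to section 6.1; if not, delete it from section 2.6. Both sections should end with the same list of weeks, week 48 included.

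The edit is one table cell, plus one clause in section 6.1 if week 28 is kept. The added testing is at most one local ELISA per participant, 140 in total, to which section 6.1 already commits the trial. No extra visit is needed, because haematology and chemical pathology samples are already scheduled at week 48.

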#### **6.1.1 Verification of HIV status of participants**

If certification is required at the request of the participant, this can be provided by the clinical team after testing at the local laboratory.

Results will always be given by a member of the study team unless the participant requests an independent physician, in which case this will be arranged.

If a specimen from a participant suggests that they are HIV infected, a second specimen will be collected and retested.

### **6.2 HIV infection**

In the unexpected circumstances that a participant in the trial acquires HIV infection, they will be managed in the following way:

#### **6.2.1 Referral for clinical care**

Participants will be referred initially to a specialist physician for a full discussion of the clinical aspects of HIV infection. Further investigations will be undertaken as necessary. Should the participant prefer to be managed at a hospital closer to their home, or by their General Practitioner, this will be arranged.

